# MObile Technology for Improved Family Planning Services (MOTIF): study protocol for a randomised controlled trial

**DOI:** 10.1186/1745-6215-14-427

**Published:** 2013-12-12

**Keywords:** Family planning, Post-abortion family planning, Contraception, mHealth, Cambodia

## Abstract

**Background:**

Providing women with contraceptive methods following abortion is important to reduce repeat abortion rates, yet evidence for effective post-abortion family planning interventions are limited. This protocol outlines the evaluation of a mobile phone-based intervention using voice messages to support post-abortion family planning in Cambodia.

**Methods/Design:**

A single blind randomised controlled trial of 500 participants. Clients aged 18 or over, attending for abortion at four Marie Stopes International clinics in Cambodia, owning a mobile phone and not wishing to have a child at the current time are randomised to the mobile phone-based intervention or control (standard care) with a 1:1 allocation ratio.

The intervention comprises a series of six automated voice messages to remind clients about available family planning methods and provide a conduit for additional support. Clients can respond to message prompts to request a phone call from a counsellor, or alternatively to state they have no problems. Clients requesting to talk to a counsellor, or who do not respond to the message prompts, receive a call from a Marie Stopes International Cambodia counsellor who provides individualised advice and support regarding family planning. The duration of the intervention is 3 months. The control group receive existing standard of care without the additional mobile phone-based support.

We hypothesise that the intervention will remind clients about contraceptive methods available, identify problems with side effects early and provide support, and therefore increase use of post-abortion family planning, while reducing discontinuation and unsafe method switching.

Participants are assessed at baseline and at 4 months. The primary outcome measure is use of an effective modern contraceptive method at 4 months post abortion. Secondary outcome measures include contraception use, pregnancy and repeat abortion over the 4-month post-abortion period.

Risk ratios will be used as the measure of effect of the intervention on the outcomes, and these will be estimated with 95% confidence intervals. All analyses will be based on the ‘intention to treat’ principle.

**Discussion:**

This study will provide evidence on the effectiveness of a mobile phone-based intervention using voice messages to support contraception use in a population with limited literacy. Findings could be generalisable to similar populations in different settings.

**Trial registration:**

ClinicalTrials.gov Identifier: NCT01823861

## Background

Globally, an estimated 44 million pregnancies end in abortion each year, of which nearly half are unsafe, resulting in 47,000 maternal deaths
[1,2]. The vast majority of unsafe abortions occur in developing countries and account for one in eight maternal deaths. Around 80% of unintended pregnancies in developing countries occur among women who have an unmet need for modern family planning (FP)
[1]. Globally, if unmet need for FP were met, an estimated 75% of unsafe abortions could be avoided
[3].

The 2010 Cambodia Demographic Health Survey (CDHS) reported that 81% of women of reproductive age did not want any more children, or wished to wait at least 2 years for their next child, but only 35% were using a modern method of contraception
[4]. Modern methods include condom, oral contraceptive (OC), injectable, implant, intra-uterine device (IUD) and permanent methods: vasectomy and sterilisation. The low use of contraception might contribute towards the high abortion rate in Cambodia, estimated at 50 per 1,000 women, well above the global average of 28 per 1,000
[5]. Furthermore, among women who have had an abortion, 26% have had more than one.

This highlights the need for more effective interventions to support clients with post-abortion family planning (PAFP).

There has been widespread uptake of mobile phones in low-income countries including Cambodia, with an estimated 19 million mobile subscriptions covering a population of approximately 14 million in 2012
[6]. Marie Stopes International Cambodia (MSIC) client exit surveys have estimated that over 80% of abortion clients own a mobile phone. The use of mobile phones to deliver healthcare (‘mHealth’) has the advantage over face-to-face healthcare delivery in that support can be delivered inexpensively wherever the person is located, when it is needed. This is of particular relevance in Cambodia where the women least likely to use a modern method of contraception are the rural poor
[4]. Behaviour change techniques (BCTs) used in face-to-face interventions can be modified for delivery via mobile phones
[7].

Previous trials related to smoking cessation and HIV have reported objective evidence of altered health behaviour leading to improved health outcomes
[8,9], yet there is more limited evidence related to the use of contraception.

Of the three previous trials in the USA to improve contraceptive use, Kirby (2010) reported no effect on contraception use with phone calls using motivational interviewing techniques
[10], and Hou (2010) reported no significant difference in mean numbers of missed pills with simple daily SMS reminders
[11]. However, in a larger trial (*n* = 962), Castano (2010) reported that participants receiving daily educational text messages and pill reminders remained more likely to continue at 6 months (OR 1.41, 1.02-1.95)
[12].

There is even less evidence for PAFP. No studies have formally reported mHealth PAFP interventions in low-income countries, although the ‘m-assist: Mobile in Medical Abortion’ trial has provisionally reported increased IUD uptake (21% *vs*. 13%) at 7 weeks post abortion with a post-abortion SMS-based intervention in South Africa
[13]. Although these study results look promising, to date, the effect of mHealth interventions on PAFP, or on a wider range of contraceptive methods, has not been reliably established.

The MObile Technology for Improved Family Planning (MOTIF) project comprises the development, implementation and evaluation of a mobile phone-based intervention to support PAFP in Cambodia. This protocol outlines our proposed evaluation of the intervention developed.

## Methods/Design

### Study design

MOTIF is a multisite single-blind randomised controlled trial (RCT). Participants are randomised to the mobile phone-based intervention (voice messages and follow-up phone calls) or standard of care (SOC)/control (no additional mobile phone-based support) with a 1:1 allocation ratio (see Figure 
1).

**Figure 1 F1:**
[figure not shown]
CONSORT diagram of study design.

### Setting and participants

Participants are recruited from four MSIC clinics; two serving predominantly urban populations around Phnom Penh City (Chbar Ambov and Takmao), and two based in provincial towns serving predominantly rural populations (Battambang and Siem Reap). Participants are eligible for the trial if they are attending for induced abortion, aged 18 years or over, own a mobile phone, do not want to have a child at the present time and are willing to receive simple voice messages from MSIC related to contraception. Clients are eligible regardless of whether they have decided to adopt PAFP after their abortion.

Potential trial participants are identified by service providers in the clinics who ask whether they would like to discuss participation in the trial with a research assistant (RA) at the end of the PAFP counselling session. RAs provide further information regarding the study. Given the high rates of illiteracy in Cambodia (literacy in rural areas was 69% according to the 2010 Cambodia DHS), the RA verbally explains the study by reading the Participants Information Sheet
[4]. If the client wishes to participate, they sign, or thumbprint, two copies of the consent form. RAs collect baseline data from participants that are recruited. The RA provides a written list of all participants recruited, together with a unique trial identification (ID) number, to the counsellor delivering the intervention. The RA sends only the ID number together with the clinic status (‘urban’ or ‘rural’) of enrolled participants to a project statistician at the London School of Hygiene and Tropical Medicine (LSHTM) via email. Participants are stratified according to urban or rural clinic status and allocated to the intervention or control group using a remote computer-based randomisation programme. Allocation is therefore concealed from RAs working on the trial.

### Intervention

The intervention was developed following a review of the literature, formative research including interviews and focus groups with abortion clients, and with input from clinicians and technology partners in Cambodia
[14].

The intervention has a similar basis to the approach used by Lester (2010) in Kenya who hypothesised that a structured mobile phone protocol to keep in touch with patient could improve HIV medication adherence
[15]. Detailed description of the intervention development will be reported elsewhere.

The MOTIF conceptual framework is based on existing literature on the determinants of contraceptive use, links between contraceptive use and fertility, and effective adherence interventions (Figure 
2)
[16,17].

**Figure 2 F2:**
[figure not shown]
Summary of conceptual framework.

The MOTIF intervention comprises a series of automated voice messages to participants’ mobile phones over the 3-month period following their abortion, at times of their preference. Clients receive the first message within 1 week of receiving abortion services and then every 2 weeks, with a total of six messages. The messages are designed to remind clients about FP methods available to them and provide a conduit for additional support. A typical message, recorded in the Cambodian (Khmer) language, is as follows:

‘*Hello, this is a voice message from a Marie Stopes counsellor. I hope you are doing fine. Contraceptive methods are an effective and safe way to prevent unplanned pregnancy. I am waiting to provide free and confidential contraceptive support to you. Press 1 if you would like me to call you back to discuss contraception. Press 2 if you are comfortable with using contraception and you do not need me to call you back this time. Press 3 if you would prefer not to receive any messages again*’

Clients who indicate they would like to talk to a counsellor, or who do not respond to the message prompts, receive a call from an MSIC counsellor. The counsellors provide individualised information on contraceptive methods and advice if the client is experiencing side effects from contraception. Clients are advised to use condoms as dual protection from HIV and sexually transmitted infections as appropriate. Follow-up calls to clients are made during preferred times indicated by the client on her registration form. Clients in the intervention arm are also able to call the MOTIF service at any time to request to speak with a counsellor. Clients who opt to receive the OC or injectable can opt in to receive additional reminder messages appropriate to their method (that is, to start a new packet of pills or when to receive a new injection). The sixth and final voice message provides similar information to the first five, but also reminds the client that this will be the last message they will receive.

The MOTIF intervention is delivered by trained counsellors at the MSIC head office in Phnom Penh. Voice messages are scheduled and sent using the open-source software programme ‘Verboice’, developed by InSTEDD (instedd.org). Verboice has functionality with all the mobile phone network operators. MSIC incurs the cost of outgoing communication from the provider to client, and clients incur any costs calling into the service (the cost of a local call). The counsellor records information on the voice messages sent, responses to messages and outcomes of follow-up phone calls.

### Control

Participants in the control group receive the current existing SOC, but not the voice messages or follow-up phone calls. Existing SOC includes: face-to-face post-abortion counselling; a clinic follow-up appointment at 1 or 2 weeks; the clinic phone number and hotline phone number: a toll-free help line for clients staffed by trained counsellors at the MSIC head office.

### Objectives

The objective of the study is to test whether additional regular, structured, interactive mobile phone-based support improves use of PAFP. We hypothesise that the intervention will remind clients about contraceptive methods available, identify problems with side effects early and provide appropriate support, and will boost motivation to use PAFP, while reducing discontinuation and unsafe method switching. Therefore we hypothesise that the intervention will increase use of PAFP compared to clients receiving SOC (control).

### Outcome measures

Baseline characteristics of study participants in both the intervention and control groups will be compared with those of the general clinic population. We will assess recruitment rates, numbers assessed for eligibility compared with numbers enrolled, and completeness of follow-up.

### Secondary outcomes

Secondary outcome measures include self-reported pregnancy, repeat abortion, contraception use over the 4-month post-abortion period (to estimate point prevalence of contraception use at any given time and contraceptive discontinuation rates), and involvement in any domestic abuse or road traffic accidents (RTA). RTAs are rare, but the only adverse health effect of cell phone use for which there is evidence
[21].

### Sample size

Analysis of 2011 MSIC clinic data indicated that the proportion of clients using an effective contraceptive method at 2 weeks post abortion was 44%. The trial will involve the same population so it is reasonable to assume similar PAFP use in the control group. Aggregate demographic and health, and Cambodian, survey data indicate that around 30% of women using hormonal methods and 10% using the coil discontinue within 1 year, many before 3 months of use
[22,23]. Contraception use, repeat pregnancy or abortion rates in MSIC clinics after 2 weeks are not known. Based on aggregate data, we anticipate 20% discontinuation from 2-week acceptance, and therefore 35% of clients will be using an effective method at 4 months post abortion.

The trial has been designed to detect an increase of 13% in contraceptive use at 4 months as results from previous mHealth HIV adherence and face-to-face contraception adherence interventions suggest that it is reasonable to anticipate an effect of this size. Canto De Cetina (2001) reported a 26% decrease in injectable discontinuation at 1 year with an intervention providing structured face-to-face counselling *versus* routine information
[24]. Lester (2010) reported a 12% increase in self-reported adherence among those receiving the mHealth intervention compared to routine care
[15].

In the four trial clinics there were over 1,500 abortions during a 3-month period in 2011, therefore even accounting for refusals and reduced recruitment due to clinic staff time pressure, we believe it will be possible to recruit 500 participants over a 3-month period. A trial of 500 has 80% power to detect a difference in contraceptive use of 35% *vs*. 48% (that is, relative risk 1.4) at the 5% significance level (that is, *P* <0.05). It is not possible to adequately power the study for the rare secondary outcomes of repeat pregnancy and abortion.

### Data collection

At present, around 50% of clients do not return to the clinic for any reason after attending for abortion, therefore all trial participants will be actively followed up by a RA to assess outcome measures. Data collection tools include baseline and follow-up questionnaires: designed in English, translated to Khmer and administered by local RAs fluent in Khmer. The baseline questionnaire contains questions to collect information on contact details, demographics, reproductive history and plans, circumstances of current abortion and mobile phone use.

The follow-up questionnaire contains questions to collect information on changes in demographics, current contraception use, contraception use over the 4-month post-abortion period, and any reported domestic abuse or RTA that could have resulted from mobile phone use. In addition to self-reported measures, clients that attend the clinic for face-to-face follow-up will be offered urine pregnancy testing and objective assessment of contraceptive use by a clinically trained RA.

The follow-up questionnaire assesses births, pregnancies, contraceptive use and discontinuation over a period of time using a similar format to that used in the CDHS.

**1. Primary**		
Use of an effective modern method of contraception at 4 months	Self-report (binary)	Chi-squared test
	Objective^a^ (binary)	
**2. Secondary**		
Pregnancy	Self-report (binary) (0, 1 or more)	Chi-squared test
	Urine pregnancy test^a^ (binary)	
Repeat abortion	Self-report (binary) (0, 1 or more)	Chi-squared test
Effective modern contraception use over 4-month period	Self-report (binary) (<80%, >80%)	Chi-squared test
Contraceptive discontinuation	Discontinuation after starting contraceptive method (time to event)	Kaplan-Meier survival analysis
Involvement in road traffic accident	Self-report (binary)	Chi-squared test
Domestic abuse	Self-report (binary)	Chi-squared test
**3. Sensitivity and per-protocol analysis**		
Participants that completed follow-up	All outcomes	Chi-squared/T-test/logistic and linear regression
Clustering among participants from one clinic		
Per-protocol analysis		
**4. Sub-group analysis**	All outcomes	
Age		
Urban *versus* rural residence		Logistic/linear regression
Level of education		
Socioeconomic status		

Follow-up at 4 months for all participants will comprise a telephone interview conducted by a research assistant.

^a^Approximately 50 participants from one clinic will be requested to attend for face-to-face follow-up for objective measurement of contraceptive outcomes.

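### Randomisation is stratified by urban/rural clinic status but the stated primary test ignores the stratum; the small loss is avoidable, and the clinic clustering row should be a clinic-adjusted analysis

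*Protocol article*

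**What the plan says.** The protocol article (Study design) makes the woman the unit of randomisation: "Participants are randomised to the mobile phone-based intervention (voice messages and follow-up phone calls) or standard of care (SOC)/control", "with a 1:1 allocation ratio". Setting and participants adds that "Participants are recruited from four MSIC clinics", two mainly urban and two mainly rural, and that "Participants are stratified according to urban or rural clinic status and allocated to the intervention or control group". Each clinic therefore lies in exactly one stratum. The Intervention section says that "The MOTIF intervention is delivered by trained counsellors at the MSIC head office in Phnom Penh", so delivery is central and not by clinic.

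Under Statistical methods, primary and secondary outcomes are to be summarised by risk ratios with 95% confidence intervals. Table 1 gives a chi-squared test for the primary outcome and for each binary secondary outcome. Neither place mentions the stratum or the clinic.

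Urban versus rural appears once more, as an exploratory subgroup factor. There it is labelled residence, not clinic status.

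Block 3 of Table 1 (sensitivity and per-protocol analysis) has a row "Clustering among participants from one clinic". The only method entry in that block is "Chi-squared/T-test/logistic and linear regression". No text explains the row, and no cluster-robust, GEE or mixed model is named anywhere.

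**The concern.** A stratified randomisation that balances the arms within strata removes the between-stratum difference from the treatment comparison. An unstratified test still counts that difference as noise, so its standard error is a little too large, its confidence interval a little too wide, and some power is lost. The subgroup analysis does not make up for this. It asks whether the effect varies with residence, which is a related but different variable, and it leaves the main estimate unadjusted.

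The clustering row raises a related question. Its label suggests a threat that this design largely avoids, because every clinic is expected to supply both arms. Its method entry does not say how clinic would be used. What is at stake is a slightly inefficient primary analysis and a sensitivity result whose meaning would depend on how the row is read.

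**Working it through.** **1. The plan's own figure.** Inputs from Sample size: 35% versus 48%, 500 women (250 per arm), 5% level, taken as two-sided.

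- Power = Φ{[0.13 − 1.96·√(2·0.415·0.585/250)] / √[(0.35·0.65 + 0.48·0.52)/250]} = 84.1% without continuity correction (225 per arm would give 80%).
- With continuity correction, 240 per arm are needed and 250 per arm give 81.8%.

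The stated 80% is therefore reproduced. It carries no design effect, which is right for individual randomisation.

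**2. Effect of leaving the stratum out.** Assumptions: equal-sized strata, arms balanced within each, overall control use 35%. The article gives no stratum rates, so these are assumed. The unstratified test uses the variance p̄(1−p̄) = 0.35·0.65 = 0.2275. The true variance of the comparison uses the within-stratum average. The actual type I error is 2·[1 − Φ(1.96/k)], where k = √(within/0.2275).

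| Use, urban / rural (assumed) | Within-stratum variance | k | Interval too wide by (1/k − 1) | Type I error |
|---|---|---|---|---|
| 35% / 35% | 0.2275 | 1.000 | 0% | 5.0% |
| 45% / 25% | (0.2475 + 0.1875)/2 = 0.2175 | 0.978 | 2.3% | 4.5% |
| 55% / 15% | (0.2475 + 0.1275)/2 = 0.1875 | 0.908 | 10.2% | 3.1% |

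Simulated trials of this design (4,000–5,000 per setting) agree. Plain chi-squared gave 4.1–4.6% in the middle row and 2.9–3.5% in the last. Tests stratified by clinic status or clinic gave about 5% (4.7–5.7% with equal clinic sizes).

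**3. Power for +13 points in both strata.** The same normal approximation, using the pooled variance for the plain test and the within-stratum variance for the stratified test, gives:

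- 35/35: 84.1% for both.
- 45/25: 84.6% plain, 85.6% stratified.
- 55/15: 86.3% plain, 90.0% stratified.

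The article states no block size. If allocation within strata is simple rather than blocked, the plain test is not conservative (4.8% in the extreme setting), but it still loses power: 84.2% against 90.0%.

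**4. Does clinic correlation inflate the error?** With a common effect, plain chi-squared had type I error of about 4.5–5.5% for clinic rates from all equal to 15/55/20/50% (assumed). The exceptions were the balanced urban/rural settings of step 2, where it was lower. There was no inflation.

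**5. Ways to carry out the clustering row with four clinics.**

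| Approach | Named in Table 1? | Type I error | Power |
|---|---|---|---|
| Logistic regression with three clinic indicators | Logistic regression is; the clinic terms are not | 4.7–5.4% | 84–89% |
| Cluster-robust errors, normal critical value | No | 13–18% | not meaningful |
| Cluster-robust errors, t on 3 df | No | 4–7% | 52–57% |

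**6. Limit of step 4.** If the true effect varies between clinics and inference is meant for a wider set of clinics, the plain test's error rises to about 8% (assumed SD of 5 points) or 20% (SD of 10 points). Clinic indicators do not cure this: they give about 9% and 21%.

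**The case against.** The strongest reply is that this is a condensed article. Stratum adjustment and the model behind a sensitivity row are commonly left to a full protocol or analysis plan, and neither is shown. That carries weight for the clustering row, which is only a label. It carries less for the primary analysis, where the article states a specific test and the test takes no account of the stratum.

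It can also be said that the gain is slight and that the plain test is valid. Both are true, and they set the weight of the point.

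A reader might go further and infer that the clustering check would be invalid, rejecting about three times too often or losing some 30 points of power. The document does not support that. Those figures belong to cluster-robust standard errors on four clinics, which it never names. Logistic regression, which it does list, works with clinic indicators. The method entry also appears to be one cell shared by several rows, so it does not show that a chi-squared or t-test is the intended clinic check.

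A reader might likewise infer that urban/rural status enters no analysis at all. It does enter, as a subgroup factor under the label of residence, and any clinic-adjusted model would absorb the stratum.

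Finally, individual randomisation does not remove variation in the effect between clinics, so looking at clinic is reasonable.

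**Conclusion.** The point holds as a modest improvement. The stated primary and binary secondary analysis does not reflect the stratified randomisation. The consequence is conservative: type I error of about 3–4.6% in place of 5% when strata differ and are balanced by arm. Stratifying would add 0–1 point of power in moderate cases and about 4 points in an extreme one, or nearer 6 if allocation within strata is not blocked. These sizes rest on assumed stratum rates, equal strata and a common effect. The primary test remains valid and 500 women remain enough.

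On the secondary point, clustering is the wrong description of what clinic does in this design under a common effect. The row needs a stated clinic-adjusted model. It cannot be called wrong beyond that.

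**What to change.** For the primary outcome, report a Mantel-Haenszel risk ratio with 95% confidence interval and a Cochran-Mantel-Haenszel test, stratified by urban/rural clinic status. Stratifying by the four clinics, which nest within that factor, is an acceptable alternative. Treat the binary secondary outcomes the same way where events are not too few.

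Reword the clustering row as an analysis adjusted for clinic as a fixed term, and show the four clinic-specific risk ratios descriptively. If logistic regression is used there, note that it yields an odds ratio, which should not be set directly beside the primary risk ratio. Do not use cluster-robust errors with four clinics.

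The cost is two lines in Table 1. Clinic status is already sent to the statistician for every woman at randomisation. In the simulations the stratified methods kept error near 5% with no material loss of power.
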